## Discussion

The main objective of this work is to investigate the efficacy of unilateral vs bilateral sequential TBS on treating MDD, the number one leading cause of disability worldwide [1]. Promising findings have shown that unilaterally delivering either excitatory- or inhibitory-inducing non-invasive brain stimulation to the left and right DLPFC, respectively, can significantly reduce MDD symptoms [46]. Other findings have shown that performing bilateral sequential stimulation, i.e., exciting the left and inhibiting the right DLPFC in the same session, is a therapy that may offer superior therapeutic effects in specific subpopulations of individuals with MDD such as people over the age of 65 [33]. Compared to HF-rTMS, TBS may be a superior non-invasive brain stimulation technique for treating MDD as it is faster and uses lower stimulation intensities [37, 38]. This naturalistic randomized large-scale non-inferiority trial is the first study investigating unilateral vs bilateral sequential TBS in treating MDD. On top of a relatively longer period of treatment, one notable strength of our study is the addition of a maintenance-phase protocol where the frequency of treatment is customized according to the individual's clinical progress. In addition, because of the heterogeneity of MDD it is expected that there will be variability of treatment response across participants. By collecting multiple symptoms using clinically valid assessments and multiple neurophysiological biomarkers – and to our knowledge, one of the largest set ever collected to date in a single study – our findings will: 1) establish whether the tested protocols (unilateral vs bilateral sequential TBS) differ in efficacy in treating MDD, 2) identify biomarkers of treatment response that are crucial to assist with participant stratification in future clinical trials, and most importantly, during participant selection for TBS treatment in clinical settings, and 3) help to elucidate CNS mechanisms through which the therapy is taking place, thus providing insight for the development of better targeted non-invasive brain stimulation protocols.

### Unilateral vs bilateral rTMS/TBS for the treatment of treatment resistant MDD

Despite the existence of effective treatments for MDD, individuals classified as treatment resistant encounter difficulties in finding suitable treatment options. Both unilateral and bilateral rTMS have shown some efficacy in treating treatment resistant MDD [34, 37, 42, 106]. However, no large-scale naturalistic study has directly compared bilateral sequential and unilateral TBS to treat MDD. This is especially important to explore considering the research trend on investigating synergetic effects of combined brain stimulation therapies. However, to date, current studies fail to identify effective bilateral brain stimulation protocols for MDD. For example, recent studies report that the effectiveness of bilateral sequential stimulation, involving HF-rTMS followed by LF-rTMS over the right and left DLPFC, did not exceed that of unilateral rTMS in reducing depressive symptoms [33, 34]. Expanding on these existing knowledge gaps, the Blumberger group reported bilateral TBS compared to standard bilateral rTMS achieved non-inferior symptom reduction for depression in individuals with a diagnosis of MDD [38]. Our study on the antidepressant effects of unilateral and bilateral TBS serves as a valuable addition to these ongoing research efforts.

### Maintenance treatment protocol

We are assessing the efficacy of a 6-month flexible maintenance phase, as previous rTMS and TBS research has shown that relapse and symptom re-emergence can occur 6 months after cessation of a successful treatment [58, 59, 109]. One rTMS study has shown that including a maintenance phase could significantly lower relapses rate in MDD, in comparison to those who did not receive maintenance treatment [59]. Though, there are very few rTMS controlled and open-label studies that have been published on maintenance after successful response to a shorter-term treatment [110], and no studies on TBS maintenance. Also, as previously suggested, the frequency and schedule of treatment administration needs to be participant-tailored and delivered based on each individual symptom severity when transitioning from the acute to maintenance treatment phases [109, 111]. Therefore, one of the important goals of this study is to determine the efficacy of a flexible maintenance TBS treatment phase that is delivered based on each participant’s symptomology and clinical development, i.e., improvement or worsening of symptoms. Participants will be evaluated with several clinically valid tests throughout the study to gain a full comprehensive data set of depressive and linked symptoms (see Table 3). This will help us to identify distinct symptom changes from the two TBS treatments (i.e., unilateral vs. bilateral).

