### Study objectives

No large-scale study has compared left unilateral versus bilateral sequential TBS for treating symptoms of MDD. The primary aim of this naturalistic, randomized double-blinded non-inferiority trial is to investigate the efficacy of unilateral (i.e., iTBS to the left DLPFC) and bilateral sequential (i.e., cTBS to the right DLPFC combined with iTBS to the left DLPFC) on reducing clinical symptoms of MDD. Based on previous research, we hypothesize that both treatments will effectively decrease depressive symptoms to a comparable degree (i.e., non-inferior) [33, 34, 61]. The incorporation of covariates during analysis may reveal a superiority of bilateral sequential TBS over unilateral treatment in specific subgroups. These subgroups include older individuals (≥ 60 years-old; [62], and/or individuals presenting with comorbid anxiety, and post-traumatic stress disorder [33, 63]). As mentioned, the clinical efficacy of rTMS is time limited [57, 58]. Therefore, this study will also investigate the efficacy of a six-month flexible maintenance phase. Additionally, to better understand the TBS-induced neurophysiological changes and their associations with therapeutic responses, multiple objectively measured neurophysiological variables will be assessed in this study. See Table 1 for a brief description of outcome measures and detailed hypotheses of this study. Ultimately, this study aims to: 1) inform whether unilateral TBS performed over the DLPFC is non-inferior to bilateral sequential TBS on treating MDD, 2) provide insight on neurophysiological mechanisms associated with treatment-induced effects and their longitudinal changes resulting from treatment, thus providing biomarkers of treatment response, and 3) explore neurophysiological markers, demographics, and clinical characteristics that may help identify responders and non-responders to treatment, paving the way for a more refined and personalized approach to TBS treatment.

**Table 1 Tab1:** Outcomes and hypotheses of the study

Outcome	Rationale	Hypothesis
Clinical (primary)	Investigate changes in severity of depressive symptoms	Unilateral TBS will be non-inferior in comparison to bilateral sequential TBS on reducing depressive symptoms

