## Methods

### Study design and overview

This is a double-blinded randomized, naturalistic, non-inferiority trial comparing unilateral vs bilateral sequential TBS (iTBS in the left vs cTBS in the right followed by iTBS in the left DLPFC, respectively). Participants enrolling in this study are referred by their physician to receive rTMS for the treatment of MDD and are randomized in a 1:1 ratio to receive either unilateral or bilateral sequential TBS. The study design and timeline of assessments and treatment schedule is presented in detail in Fig. 2.

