The TBS treatment will be administered by trained research personnel 5 days a week (Monday-Friday) over the first 4 weeks (initial treatment phase; Fig. 2B). Participants who do not achieve remission (i.e., non-remitters) after the initial treatment phase as per the 17-item Hamilton Rating Scale for Depression (HRSD-17; score of > 7) will undergo two additional weeks of treatment (totaling 6 weeks of initial treatment) (Fig. 2C). The additional two weeks provides an opportunity for individuals, particularly older adults, who require a longer period to achieve response from stimulation treatments [89]. Participants who do not respond to treatment (i.e., < 50% decrease in pre-treatment HRSD-17 score) after the two additional weeks of full treatment will be discharged from the study and treatment recommendations will be provided to their referring physician by the study psychiatrist. Participants who show remission at week 4 or response at week 6 will enter a six-month maintenance phase, where treatment will be determined based on their symptomatology (Fig. 2D and E). In the first 4 weeks of this phase, participants will be remotely assessed for clinical outcomes (phone or video-call) once per week (e.g., on Mondays) and treatment will be administered 2x/week (e.g., every Wednesday and Friday). In the following 8 weeks (i.e., weeks 9–16) treatment frequency will be further decreased, and the HRSD-17 score, remotely assessed weekly on Mondays, will determine the number of treatment sessions that week. Participants can receive 0, 1, or 2 treatment sessions, as follows: a) no TBS session, if HRSD-17 score of ≤ 8 (no depression) or a < 3 point increase from their final initial treatment HRSD-17 score; b) 1 TBS session, if their HRSD-17 score increased by ≥ 3 and < 8 from their final initial treatment HRSD-17 score; c) 2 TBS sessions, if their HRSD-17 score increased by ≥ 8 from their final initial treatment HRSD-17 score [60]. From week 17–25, participants will be clinically assessed on Mondays of every second week to determine whether they will receive 0, 1, or 2 TBS sessions that week based on the same criteria previously mentioned. Finally, in week 28 participants will complete clinical assessments and TMS-EEG on Monday and Friday, respectively, they will not receive TBS treatment.

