Throughout the study participants will be reminded of the importance of following study guidelines and adhering to the treatment schedule. Study staff will do their best to accommodate for participants' schedules and mitigate conflicts keeping them from adhering to the study protocol. Missed treatment sessions (e.g., due to illness or scheduling conflicts) will be made up for at the end of the treatment phase to ensure the proposed total number of treatment sessions are completed. Participants will be discharged from the study if they are non-adherent, i.e., fail to attend or are absent for > 3 consecutive treatment days or 15% of sessions during the treatment phase. Missed treatments relating to Covid-19 related symptoms will not be counted towards this criterion. Participants will also be discharged if they have a sustained relapse in the maintenance phase of the study, i.e., requiring two treatments per week for more than two consecutive assessments.

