### Randomization and blinding

Participants are randomized (1:1 ratio) using the study randomizer software (https//www.studyrandomizer.com). A permutated block is used to randomize participants into the treatment groups. Participant stratification is based on the following variables: 1) age (< 65 or ≥ 65 years-old), 2) depression (unipolar or bipolar), 3) comorbid generalized anxiety (yes or no), 4) comorbid post-traumatic stress disorder (yes or no), and 5) biological sex (male or female). Upon entering these participant characteristics, the software provides a number (e.g., 0 or 1) that corresponds to a treatment group in which experimenters and participants are blinded to. Participants will remain assigned to their designated group until the treatment concludes.

This study is a two-arm double-blind trial as neither the participants nor the outcome assessor, care provider and data analysts will know the condition assigned to the participants. The master randomization list of the treatment blinding will be kept by a scientist of the research centre that is not involved in the project. This can be broken in case of emergency (e.g., severe adverse events such as seizure induced by treatment) and they can then inform required medical professionals directly if necessary. Directly involved research staff will be blinded (including the principal investigator and study psychiatrists).

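### The stated aim of determining the efficacy of flexible maintenance TBS cannot be met, because all eligible participants enter one maintenance programme with no comparator; the aim should be descriptive

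*Protocol article*

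**What the plan says.** The aim appears twice in the protocol article. Under Study objectives: "this study will also investigate the efficacy of a six-month flexible maintenance phase". In the Discussion, under Maintenance treatment protocol: "one of the important goals of this study is to determine the efficacy of a flexible maintenance TBS treatment phase".

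The design is set out in Methods, under Study design and overview (including the Fig. 2 caption), and under Randomization and blinding:

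- **Entry.** "Participants who show remission at week 4 or response at week 6 will enter a six-month maintenance phase". Those without response after the two additional weeks are discharged.
- **Treatment in the phase.** For the first four weeks every entrant has two sessions a week. After that, "the HRSD-17 score, remotely assessed weekly on Mondays, will determine the number of treatment sessions that week", and from week 17 the same rule applies at fortnightly assessments.
- **Exit.** Sustained relapse, defined as "requiring two treatments per week for more than two consecutive assessments", leads to discharge.
- **Randomisation.** Participants are "randomized in a 1:1 ratio to receive either unilateral or bilateral sequential TBS", and "Participants will remain assigned to their designated group until the treatment concludes". No later allocation is described.

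The Limitations section does not mention a missing control for maintenance. The Strengths section lists the maintenance phase as a strength.

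**The concern.** Efficacy is a causal claim: outcomes with flexible maintenance are better than they would have been without it, or under some other schedule. To support it, a design needs a group that shows what happens otherwise. This trial has none for the maintenance question.

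If few participants relapse, four explanations remain open: the maintenance sessions, the natural course after a successful acute phase, the selection of people who had already responded, and the medication that participants are required to keep stable. The data cannot separate them. The Discussion says that no studies of TBS maintenance exist, so a low relapse rate reported here as efficacy would probably be cited as the first evidence on the question.

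**Working it through.** The article gives no figure for maintenance, so there is none to reproduce. The check is to follow the design and see which contrasts it contains.

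**Step 1. Who enters.** Inclusion requires HRSD-17 ≥ 15, and remission is HRSD-17 ≤ 7. The smallest possible reduction in a remitter is (15 − 7)/15 = 53%, which meets the 50% response criterion. So every entrant, whether a week-4 remitter or a week-6 responder, is a responder. The entry rule sends all of them into maintenance and sets none aside.

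**Step 2. Which contrasts exist among entrants.**

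| Contrast needed for an efficacy claim | Present in the design? |
|---|---|
| Maintenance against no maintenance | No |
| Active against sham maintenance | No; both arms keep active left iTBS, and only the right-sided stimulation differs |
| Flexible against fixed schedule | No; both arms follow the same rule |
| Historical or external control | None described |
| Unilateral against bilateral | Yes, but it concerns stimulation type |

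**Step 3. What the surviving contrast can do.** Allocation is kept into maintenance, so arms can be compared there. But entry depends on response, which occurs after randomisation and may depend on the arm. Entrants in the two arms are therefore not protected by randomisation, and even a fair comparison would say nothing about maintenance as such.

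**Step 4. What the planned models contain.** Under Effectiveness of TBS treatment, the terms are time (pre, post) and time by arm. No term represents a maintenance strategy, and with one strategy none could be estimated.

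**Step 5. What the protocol's own evidence used.** In the Background, the halving of relapse comes from a randomised study in rTMS responders, and the case for flexible scheduling comes from ECT research that compared it with treatment given regardless of symptoms. The Discussion cites lower relapse relative to people without maintenance. Each had the kind of comparator missing here.

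**Step 6. What can be estimated.** A relapse proportion has an approximate 95% half-width of 1.96 × √(p(1 − p)/n), widest at p = 0.5. The response rate is an assumption. The range 25% to 56% borrows the two rates that the Sample size section quotes from a 32-participant study using a different scale. Participant numbers run from 158 (the calculated sample) to 256 (the cap).

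- Low end: 158 × 0.25 ≈ 40 entrants; 1.96 × √(0.25/40) = 0.155.
- Middle: 158 × 0.50 = 79 entrants; 1.96 × √(0.25/79) = 0.110.
- High end: 256 × 0.56 ≈ 143 entrants; 1.96 × √(0.25/143) = 0.082.

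These widths describe the precision of a descriptive result. They do not measure the defect, which no increase in n removes.

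**The case against.** The best reply is that this aim carries little weight. It is one sentence in Study objectives plus Discussion prose. It is absent from the three numbered aims, from Table 1, from the primary and secondary outcome definitions and from the sample size calculation, and the Sample size section calls all other tests exploratory. The trial also describes itself as naturalistic. All of this stands and limits the consequence. It does not remove the mismatch: the text says efficacy, and the Discussion calls the goal important. Nor is this a detail for an analysis plan, since no analysis can supply a control group.

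A reader might infer more than the document supports:

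- **Confounding by indication.** After the first four weeks, sessions are given because symptoms worsen, so relating session count to outcome would mislead. But no such analysis is planned, and symptom-driven dosing is itself the strategy under study. The obstacle is the missing comparator.
- **Final-visit scores describe only survivors.** Relapse does lead to discharge. But the Data analysis section keeps everyone as randomised and treats discharge as missing data to be managed, the Participants section plans extended data collection after discontinuation, and the mixed models allow for missing values. Whether this is enough can be debated; it cannot be asserted that the problem was ignored.
- **A responder-only arm comparison presented as randomised.** The article specifies none. The Discussion expects to see distinct symptom changes from the two treatments, but from assessments throughout the study. A label in advance is still worthwhile.
- **The maintenance data are worthless.** They are not; they can be read descriptively.

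**Conclusion.** The concern holds for the wording of a secondary aim. As designed, the trial can describe relapse, symptom course and session use under flexible maintenance in acute-phase responders. It cannot determine whether maintenance works, or whether a flexible schedule does better than another, at any sample size. The conclusion rests on the entry rule, the single randomisation and the common session rule, all stated in the article. It assumes only that the article has not left out a maintenance control group, which is unlikely given how fully it describes the phase. The entrant numbers and half-widths (about 40 to 143 entrants, about ±16 to ±8 points) depend on assumed response rates, and the conclusion does not depend on them. It would be wrong to read this as a flaw in the unilateral against bilateral non-inferiority comparison, which is made on the acute phase and is unaffected.

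**What to change.** Five changes of wording, none of which alters any participant's treatment:

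1. In Study objectives and in the Discussion section on maintenance, replace the efficacy aim with a descriptive one: estimate, with 95% confidence intervals, the sustained-relapse rate (as already defined in Methods) and the number of sessions used among acute-phase responders.
2. State that participants discharged for sustained relapse count as relapsed in that rate.
3. State that no efficacy claim for maintenance will be made.
4. Label any between-arm comparison among maintenance entrants as exploratory, because entry depends on response after randomisation.
5. Add the missing maintenance comparator to the Limitations section.

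The cost is a few sentences and a less ambitious claim. No new data and no change to the primary analysis are needed.

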### Brain biomarkers – assessing CNS effects and predicting treatment response

In clinical research, efforts have been recently made to improve upon the practice of delivering treatments in a ‘*one size fits all*’ perspective [44]. This is the reason why exploring cross-modal biomarkers (e.g., clinical characteristics/neuroimaging/neurophysiology) is highly encouraged in clinical trials as they would help to identify participants who would and would not benefit from treatment, and provide insight on the underlying cause behind the different responses [44, 112, 113]. We expect that not every participant will respond clinically to the TBS treatments [114, 115], therefore investigating biomarkers is an important aspect of this study. The multiple neurophysiological and neuroimaging experiments collected will help us to identify predictors of response that could serve to guide participant selection for TBS treatment, and guide future non-invasive brain stimulation research on the development of novel protocols for participants profiled as non-responders.

Biomarkers indexing effectiveness of non-invasive brain stimulation protocols traditionally rely on investigation of corticospinal excitability assessed by TMS-evoked MEPs. Analysis of its EMG features provide indexes of excitatory and inhibitory receptor activity involved in LTP and LTD [116, 117], processes of strengthening and weakening synaptic connections, respectively, in which neuroplasticity relies [118]. Several studies have shown that, although probed in the motor cortex (M1), MEPs are associated with functionality and symptoms inside and outside motor regions, such as cognition, migraines, sleep deprivation, cognitive impairment, pain, and others [117, 119–124]. For this reason, assessment of MEPs is largely used in research attempting to understand CNS-induced changes resulting from various interventions and, especially, to provide biomarkers of disease, symptom progression, and recovery in the lesion-disrupted brain (e.g., stroke, Multiple Sclerosis, Alzheimer’s, Parkinson’s, mild cognitive impairment, and others [116, 117, 125–127]).

In our study, we are performing typical single- and paired-pulse TMS experiments to assess biomarkers of intracortical inhibition and excitation that are primarily, but not exclusively, mediated by GABAergic and glutamatergic neurotransmission, respectively [97]. Specifically, we will collect motor thresholds (RMT and AMT), biomarkers of cortical excitation (MEP amplitudes and ICF), and biomarkers SICI and LICI [97]. These biomarkers are of particular importance since previous TMS studies have shown that they are sensitive to abnormalities associated with MDD and related symptoms (e.g., cognitive impairments, mood alterations) [128]. For instance, studies investigating TMS motor thresholds in depressive disorders have shown reduced corticospinal excitability in the left cortex [129, 130] and interhemispheric imbalance, i.e., lower and higher excitability in the left and right cortex, respectively [131]. Delivering rTMS to excite the DLPFC has shown to revert this lowered excitability and reduce interhemispheric asymmetries, effects that were associated with clinical improvements [50]. As for the TMS biomarkers indexing GABAergic-mediated corticospinal inhibition (e.g., SICI, LICI) [97], previous studies have suggested a possible cortical disinhibition (i.e., decreased SICI) in the left hemisphere in MDD [132, 133]. These findings are interesting since outside pathology, excitation and inhibition are not mutually exclusive; lower excitation is typically followed by higher inhibition and vice-versa [64]. The fact that this does not seem to be the case in MDD points to the value of TMS-assessing both inhibitory and excitatory circuitry for a better comprehension of the treatment induced-neurophysiological effects and to identify complementary biomarkers of treatment response in MDD. The limitation of relying solely on TMS-induced MEPs to investigate the effects of interventions not focusing on the motor cortex (i.e., focusing on the DLPFC) is that this brain region is not amongst the most relevant CNS structures involved in symptoms of MDD and is not the targeted brain region of this treatment. Complementary to MEPs, we hope to improve our treatment predictability by including other neurophysiological assessments such as TMS-EEG and MRI. These techniques will help us to investigate the TBS-induced neurophysiological changes within the treatment-targeted region (i.e., DLPFC) and connected CNS structures closely associated with depressive symptoms (e.g., ACC).

For instance, a previous TMS-EEG study has shown higher intracortical inhibition (e.g., N45 and N100 amplitude) in the DLPFC of individuals with a diagnosis of MDD in comparison to healthy controls. N45 amplitudes were also predictive of a higher degree of depression [64]. By looking at other events of TEPs (e.g., P60, a biomarker of intracortical excitation) these authors also reported higher excitation and an excitation/inhibition imbalance in the DLPFC of individuals with a diagnosis of MDD in comparison to healthy controls, and a further abnormal lack of association between excitation and inhibition in MDD, an association that is present in the healthy brain [64]. Abnormalities in neurophysiological features in MDD have shown to be associated with diminished capacity for neuroplasticity, which in turn, has been associated with a higher degree of MDD symptoms and relapses [128]. Ge et. al (2022) showed that the first treatment session of rTMS-inhibitory stimulation delivered to the right DLPFC induced acute widespread changes in functional connectivity measured by fMRI (i.e., TMS-fMRI) [134]. Interestingly, these authors reported that this first acute rTMS-induced plasticity response, but not resting state fMRI, was predictive of clinical outcomes (determined by MADRS scores) collected 4 weeks later, after cessation of daily rTMS treatment [134]. Most recently, in a subset of MDD participants who completed the Blumberger trial, Strafella, et al. (2023) reported that both iTBS and HF-rTMS reduced N100. Interestingly, participants who responded to treatment had higher baseline N100 and higher N45 post treatment when compared to non-responders [135]. Taken together, these findings provide support for the link between the neurophysiological effects of TBS and treatment effectiveness. Therefore, we will use TMS-EEG to investigate trans-synaptic activation of local and distal cortical networks mediated by excitatory and inhibitory cortical circuitry [48]. One novelty of our TMS-EEG method is the additional investigation during treatment, which has never done before and could complement the existing pre-post findings and could identify new neurophysiological markers of TBS response. As well, like Ge et. al (2022) we will assess the widespread TBS treatment-induced plasticity throughout treatment (see Table 3 for time points) [134]. This will be done to investigate whether the first treatment-induced plasticity is predictive of outcomes and whether the longer-term treatment can restore the diminished plasticity in MDD. As well, we will include additional neuroimaging techniques assessed during baseline, MRS and resting state fMRI, to investigate the availability of neurotransmitters (GABA and glutamate) within the ACC and connectivity between CNS structures, respectively. Both of these techniques are popular in MDD research and have shown to be sensitive to identifying abnormal neurophysiological features in MDD (for review see [136, 137]).
